#### History of disability diagnosis

One item will assess the lifetime history of diagnosed disability (autism or Asperger’s syndrome, intellectual disability, specific learning disability, Tourette syndrome, cerebral palsy, acquired brain injury, other neurological disability, hearing impairment, visual impairment).

#### Pubertal development

A separate set of questions for females and males will be used to assess pubertal development (e.g., ‘at what age did you get your first period/did your voice begin to break?’). Participants will also be provided with line drawings of stages of pubertal development (Tanner Stages) and asked to rate their current stage of physical development against these images.

#### Bullying

Bullying items were drawn from previous school-based trials. The three items examine whether participants have been bullied, have been cyber-bullied or have bullied others in the past 12 months. Items are responded to on a 5-point frequency scale from 1 (‘Not at all’) to 5 (‘Most days’).

#### App use and feedback surveys

App use and feedback surveys for both the Future Proofing app and the SPARX app will be administered at the post-assessment time point. The Future Proofing App Survey was developed for this study and has nine items which assess app task preferences and reasons for discontinued use. The SPARX Feedback Survey is an 11-item survey that has been used previously to assess SPARX use [23] and app acceptability, and asks participants to select any skills they learnt from using the app.

### Smartphone-collected data

Additional data will be collected directly via smartphones through a study app developed for this study (the Future Proofing App), as these data cannot be collected from the self-report questionnaires outlined earlier. Three forms of data will be collected, which include actively collected data, passively collected data and app usage data. Actively collected data will assess self-reported mood ratings, voice samples and cognitive tasks. This form of data will overcome biases in retrospective reporting of mood and allow for an investigation of whether changes in voice are related to changes in mental health states. Cognitive tasks include two measures of executive function presented in affective and neutral contexts. Specifically, a measure of affective shifting [82] and the Affective Digit Span [83] and a typing speed task, which will allow for a mechanistic assessment of the way cognitive function affects psychological outcomes in adolescents.

Passively collected smartphone data will involve the collection of location data (GPS) and movement data (accelerometry), which will be used to investigate whether mental health changes can be predicted from location and activity data. Smartphone sensor data will be collected during the first 3 months of the study, and at each annual assessment point for 3-month periods. App usage data will allow for assessment of app use and completion, and time spent using the study app/s.

### Linked data

Data relating to participants’ academic outcomes, physical health, utilisation of health services, infant development, births and deaths will be linked from extant Australian government administrative datasets by an authorised agency of the New South Wales Ministry of Health, the Centre for Health Record Linkage (CheReL, www.cherel.org.au). Informed consent from each participant will be obtained prior to linkage and databases will be linked using personal identifiers such as names, dates of births, addresses and hospital identification numbers with probabilistic methods. Linked data will be provided to the researchers in a de-identified manner and will be used to determine related health and other outcomes for the participant, including birth and perinatal data, educational outcomes in standardised curriculum-based tests, and hospitalisation and mortality outcomes. Linkage will occur within the first 12–24 months of the study (at the end of 2020) and will be updated periodically every 2 years until the trial concludes.

### Procedure and participant timeline

Figure 1 shows the participant timeline and flow. An initial preparatory phase and first school visit will solicit parental and student consent, ensure that electronic study questionnaires are accessible by consented students and ensure that the appropriate study apps are installed on each student’s device. Each subsequent school visit will coincide with an assessment occasion. During these visits, students will access study questionnaires via a secure online portal, accessible using their mobile number and a one-time password sent via SMS. Study personnel will attend these school visits to assist with technical issues and participants’ questions. Following completion of baseline questionnaires, participants in the intervention condition will be instructed to commence the intervention both during class time and in their own time, and will receive notifications and reminders over the following 6 weeks to do so. Schools are required to schedule four 20-min in-class sessions for intervention completion but may choose to hold additional sessions (up to seven). Participants in the control condition will also be provided with equivalent class time to complete activities on the Future Proofing app. Students who do not complete assessments in school will also have the option to do this in their own time. Students will have up to 4 weeks following the scheduled assessment date to complete questionnaires at each time point, after which the assessment surveys will be locked and no longer accessible. During this 4-week window, automated electronic reminders will be sent to students to prompt completion, if required.

### Sample size

Separate sample size estimates were derived to determine the numbers of participants needed to meet the aims of each trial stage. Power was set at 0.80, α = 0.05 (two-tailed), and a correlation of 0.5 assumed between baseline and endpoint symptom scores. To account for possible clustering effects at Stage I (i.e., participants from the same school having prognostically relevant characteristics and outcomes more alike than between schools), a design effect [84] was calculated assuming an intraclass correlation coefficient (ICC) of 0.03 (based on previous school-based studies) [85] and a cluster size of 50 students, yielding a design effect of 2.47. In order to detect a mean standardized difference of 0.3 between conditions at Stage I, a sample of 870 participants would be needed (435 per arm). Allowing for up to 30% attrition, recruitment of 1244 participants would be required (622 per arm).

Using similar parameters for Stage II (without a design effect) would require recruitment of 368 participants in total to detect the same effect size. However, participants in this stage must meet eligibility requirements regarding elevated symptoms and failure to respond to the first-stage intervention. They must also be willing to participate. Accordingly, a scenario involving recruitment of 10,000 participants at Stage I was considered, assuming 7000 participants would have endpoint data available at 12 months (allowing for 30% attrition). Conservatively estimating 20% having PHQ-A scores ≥ 10, 25% showing a reduction due to the Stage I intervention and that 50% of those eligible to enrol at Stage II do so, 525 participants would enter this stage II, with endpoint data available for at least 368 (allowing for up to 30% attrition). This sample would enable the detection of differences in changes in symptomatology scores of comparable size to those in Stage I of the trial (*d* = 0.29).

Given that a target sample of 10,000 is substantial, if the numbers of participants are not sufficient to reach the Stage II target, then supplementing this sample with additional young people specifically targeted based on PHQ-A scores that fall in the top 20% of population scores to ensure that this stage of the trial has comparable power to Stage I to detect an intervention effect will be considered. This will ensure that sufficient numbers are included at both stages of the trial. Should the target be met, Stage I of the trial will have much higher power to detect changes in symptom scores and would be adequately powered to detect differences in incidence based on PHQ-A diagnosis criteria.

Exploratory analyses for moderating and mediating effects will be feasible at both stages. Stage II will have power to detect small to medium mediation effects [86]. Power to detect medium-size effects (0.5 SD) in moderation analyses will be maintained for subgroups down to approximately 120 participants. Power will be enhanced in longitudinal modelling (growth curves) which use multiple occasions of measurement to estimate rates of change [86].

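### The Stage II figure of 368 is given once as a recruitment requirement and once as a number with endpoint data; only the second fits the plan's own method, and detecting d = 0.3 needs about 503 recruited

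*Protocol article*

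**What the plan says.** All of this is in the protocol article, Methods, Sample size.

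- **Common inputs.** "Power was set at 0.80, α = 0.05 (two-tailed), and a correlation of 0.5 assumed between baseline and endpoint symptom scores".
- **Stage I.** "In order to detect a mean standardized difference of 0.3 between conditions at Stage I, a sample of 870 participants would be needed". The design effect comes from an ICC of 0.03 and "a cluster size of 50 students, yielding a design effect of 2.47". The plan then allows for 30% attrition and arrives at 1244 to be recruited (622 per arm). The number needed and the number recruited are kept apart.
- **Stage II, requirement.** With similar parameters and no design effect, the plan "would require recruitment of 368 participants in total to detect the same effect size".
- **Stage II, projected yield.** From 10,000 recruited at Stage I, the plan projects 525 entering Stage II, "with endpoint data available for at least 368 (allowing for up to 30% attrition". It gives the detectable effect for this sample as d = 0.29.
- **Supplementation.** The following paragraph says that adding young people with high PHQ-A scores will be considered "if the numbers of participants are not sufficient to reach the Stage II target". Its stated aim is to give Stage II power similar to that of Stage I. It does not say which number is the target.

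**The concern.** One number is given two roles that differ by the attrition allowance. If 368 must be recruited and 30% are lost, fewer than 368 have endpoint data. If 368 must have endpoint data, more than 368 must be recruited. The Stage I text shows that the authors use recruitment for the figure after inflation for attrition, so the Stage II sentence cannot be put down to a different use of the word.

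At stake is the figure that a trial team would use to judge whether Stage II is large enough. The supplementation paragraph relies on a target, and the only sentence that says what Stage II requires is the one giving 368 recruited. If entry to Stage II falls short of 525, a team could take 368 entrants as sufficient.

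**Working it through.** **Inputs, all from the Sample size section except the last:** power 0.80; two-sided alpha 0.05; baseline-endpoint correlation r = 0.5; d = 0.3; Stage I design effect 2.47; attrition 30%; 1:1 allocation (Randomisation section).

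**Method.** Two-sample comparison of change scores. In baseline SD units, the SD of change is √(2(1 − r)) = √(2 × 0.5) = 1. Then n per arm = 2(z₀.₉₇₅ + z₀.₈₀)² × SD² / d².

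**Step 1: reproduce Stage I.**
- n per arm = 2 × (1.960 + 0.842)² / 0.3² ≈ 174.5, so 175. With the t distribution it is 175.4, so 176.
- 176 × 2 × 2.47 = 869.4, so 870 (435 per arm), as stated.
- 435 / 0.7 = 621.4, so 622 per arm and 1244 in total, as stated.

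**Step 2: the same method for Stage II at d = 0.3, without the design effect.**
- With endpoint data: 2 × 176 = 352 (350 by the normal formula).
- Recruited: 352 / 0.7 = 502.9, so about 503 (504 with equal arms). Cross-check from the plan's own Stage I total: 1244 / 2.47 = 503.6.

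**Step 3: test each role of 368.** Power = Φ(d / √(2/n) − 1.960), with n per arm; the t-based result is alongside.

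| Role of 368 | With endpoint data | Per arm | Power at d = 0.3 (normal / t) | Detectable d at 80% power |
|---|---|---|---|---|
| Number with endpoint data | 368 | 184 | 82.1% / 81.9% | 0.293 |
| Number recruited, 30% lost | 368 × 0.7 = 257.6, about 258 | 129 | 67.3% / 67.0% | 0.350 |

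The first row matches the stated d = 0.29. It also matches the projected yield: 10,000 × 0.7 × 0.20 × 0.75 × 0.50 = 525, and 525 × 0.7 = 367.5, about 368. The second row matches nothing that the plan states.

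**Step 4: could another method make 368 a recruitment figure?** Baseline adjustment (ANCOVA) multiplies the outcome variance by 1 − r² = 0.75. That gives 131 per arm, 262 with endpoint data and 262 / 0.7 = 374 recruited, which is close to 368. With 368 recruited (129 per arm), power would be about 79%. But the same method would put Stage I at 262 × 2.47 = 647, not 870, and the detectable effect with 368 analysed at 0.25, not 0.29. The plan's other figures therefore exclude it.

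**The case against.** The strongest reply is that the paragraph largely corrects itself. It goes on to give the full chain of 525 entering, 368 with endpoint data and d = 0.29, and that chain is sound on this point. Nowhere does the plan propose to recruit 368 and lose 30% of them. This stands.

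A reader might infer that Stage II is planned at 67% power, or that supplementation would be blocked once 368 had entered. The documents support neither. The 67% arises only if the undefined target is taken as 368 recruited. Supplementation is something to be considered, with no automatic trigger, and its stated aim of matching Stage I power would argue against stopping at 368 entrants.

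The two readings of the target also part only when entry falls between 368 and about 503. At 525 both are met, and below 368 both are missed.

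It can also be said that the plan promises similar rather than identical parameters, and that 368 may not have come from the 525 projection. Its origin is indeed an inference. But the one alternative method that brings the recruitment sentence close fails against 870 and 0.29.

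Finally, a mixed model can use participants with incomplete data, so 258 is a count of those with endpoint data and not of everyone analysed. The plan's own sample size method counts those with endpoint data, and the comparison here follows it.

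What remains is a stated requirement that is wrong as written, and a target that relies on it without a definition.

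**Conclusion.** The point holds as an error in a stated sample size. By the method that yields the plan's Stage I figures, 368 is a number with endpoint data. The recruitment figure for d = 0.3 is about 503, which is 37% higher (503 / 368 = 1.37). The planned scenario of 525 entrants is not affected: it gives about 82% power at d = 0.3.

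The practical risk is conditional. If the Stage II target were taken as 368 recruited and 30% were lost, about 258 would have endpoint data, power at d = 0.3 would be about 67%, and the detectable effect would be about 0.35. That falls short of the Stage I-level power that supplementation is meant to secure.

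These figures assume the stated r = 0.5, 30% attrition, equal arms and a change-score comparison. Whether 525 entrants can be reached is a separate question and is not judged here.

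**What to change.** Two changes to the Sample size section.

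1. Replace the Stage II requirement with wording such as: Stage II needs about 352 participants with Stage II endpoint data to detect d = 0.3, that is, about 503 recruited allowing for 30% attrition; the 525 projected entrants, giving about 368 with endpoint data, correspond to d = 0.29. Keep the term endpoint data as the section has it. The Hypotheses section names both a pre-to-post and a 12-to-24-month comparison for Stage II, and this correction should not choose between them.
2. In the supplementation paragraph, define the Stage II target as a number recruited, at least 503.

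The cost is wording only, with no change to the design. The drawback is that the stated recruitment requirement rises from 368 to about 503, which leaves little margin below the projected 525 (525 − 503 = 22).

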This SPIRIT-compliant protocol describes the methodology for a multi-stage, two-arm, parallel group RCT (Additional file 1). At Stage I, a cluster RCT will be undertaken to evaluate the effectiveness of SPARX, which is an app-based CBT gaming intervention [29]. This intervention has been tested in the Australian adolescent population and was found to be effective for the prevention of depression [23]. In the current trial, SPARX will be delivered to Year 8 students (who are typically aged 12–14 years). The control group will consist of Year 8 students of an equivalent demographic who will not receive any intervention. Participants across both arms will be followed longitudinally over 5 years. The choice to use a non-active (treatment-as-usual) comparator was made to avoid placing unnecessary burden on the participants and schools, which would have been required to provide an attention-matched placebo intervention—an intervention that would have required an equivalent level of effort to that of the active condition—that would most likely provide no benefit. Other candidate programmes that may have benefited other outcomes such as lifestyle or nutrition programmes could not serve as a fair control condition because of their likely impact on mental health. At Stage II (12 months following baseline), an individual-level RCT will be conducted within the intervention arm. Individuals who show elevated symptoms of depression at 12 months will be randomised to an intervention condition that receives a second CBT app which targets sleep difficulties (Sleep Ninja) or a control condition. Sleep Ninja focuses on sleep disturbances and delivers cognitive behaviour therapy for insomnia (CBT-I). An intervention targeting sleep difficulties was selected because sleep disturbance is both a risk factor and a symptom of depression, with efficacy supporting its use in the prevention and treatment of depression in both adults and adolescents [28, 30–32].

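### The Stage II sample size is worked from both Stage I arms, although Stage II recruits only from the SPARX arm, so the stated entrants and completers are about twice what the design yields

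*Protocol article*

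**What the plan says.** The current study (Background) states that at 12 months "an individual-level RCT will be conducted within the intervention arm". The Abstract and the Hypotheses section say the same in other words. The Interventions section describes Sleep Ninja as meant for students with raised symptoms a year after the universal programme. Trial design and Randomisation give 1:1 allocation at Stage I, by school.

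The Sample size section sets 80% power, two-sided alpha of 0.05 and "a correlation of 0.5 assumed between baseline and endpoint symptom scores". Stage I is sized to "detect a mean standardized difference of 0.3 between conditions at Stage I". Stage II, with no design effect, "would require recruitment of 368 participants in total to detect the same effect size".

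The section then takes 10,000 students at Stage I and 7,000 with 12-month data. It assumes 20% with PHQ-A of 10 or more, 25% of these improved by the Stage I intervention, and half of the eligible enrolling. It concludes that "525 participants would enter this stage II, with endpoint data available for at least 368" after 30% attrition, which it says allows detection of "differences in changes in symptomatology scores of comparable size to those in Stage I of the trial" (d = 0.29).

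If Stage II falls short, the section says that adding young people selected on PHQ-A scores will be considered.

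**The concern.** The chain of rates begins with every student followed to 12 months, control students included. Control students cannot enter Stage II as designed: they are in the wrong arm, and they cannot have failed to respond to an intervention they did not receive, which the Sample size section itself makes a condition of entry. No step in the chain takes the SPARX half.

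Stage II is a randomised trial with its own hypotheses, and its numbers are the reason given for considering 10,000 students; by the same section Stage I needs only 1,244. If the chain is out by a factor of two, the stated Stage II power is not reached even when recruitment succeeds in full. The supplementary recruitment, worded as a contingency, then becomes something to expect.

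**Working it through.** **Inputs (all from Sample size unless noted).** Stage I recruits 10,000; retention 0.70; raised PHQ-A 0.20; remaining after Stage I response 0.75; enrolment among the eligible 0.50; Stage II retention 0.70; r = 0.5; d = 0.3; alpha 0.05 two-sided; power 0.80. SPARX share one half (1:1 allocation, Randomisation).

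**Step 1: reproduce the plan's figures.**
- Entrants: 10,000 × 0.70 × 0.20 × 0.75 × 0.50 = 525.
- With endpoint data: 525 × 0.70 = 367.5, rounded to 368.
- SD of change in units of the score SD: √(2(1 − 0.5)) = 1. Detectable d: (1.960 + 0.842) × √(4/368) = 0.292, the stated 0.29.

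All three match, so the starting point was the 7,000 of both arms and the variance was that of a change score.

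**Step 2: repeat from the SPARX arm only.**

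| Step | As stated (both arms) | As designed (SPARX arm) |
|---|---|---|
| With 12-month data | 7,000 | 3,500 |
| × 0.20 raised PHQ-A | 1,400 | 700 |
| × 0.75 not improved | 1,050 | 525 |
| × 0.50 enrol | 525 | 262.5 |
| × 0.70 with endpoint data | 367.5 | 183.75 |

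**Step 3: consequence for power (two-sample comparison of change).**
- 368 completers: power for d = 0.3 is 82%; detectable d is 0.29.
- 184 completers: power for d = 0.3 is 53%; detectable d is (1.960 + 0.842) × √(4/184) = 0.413, about 0.41.
- 184 completers with baseline adjustment (variance factor 1 − 0.5² = 0.75): power is 65%; detectable d is 0.413 × √0.75 = 0.36.

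At these rates, 525 entrants from the SPARX arm need 525 / (0.5 × 0.70 × 0.20 × 0.75 × 0.50) = 20,000 Stage I students.

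**Step 4: the two uses of 368.** A two-sample t calculation for d = 0.3 at 80% power gives 176 per arm, 352 in total. As a check, 352 × 2.47 = 869, against the 870 stated for Stage I. At 30% attrition, 352 completers require 352 / 0.70 = 503 recruits. The section gives 368 first as the number to recruit and then as the number with endpoint data. The stated inputs yield it as neither requirement; it appears only as the end of the chain in Step 1.

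**Step 5: other readings tried.**
- Taking the 0.50 as the arm split: 3,500 × 0.20 × 0.75 = 525, but everyone eligible would have to enrol, and the text defines the 50% as uptake.
- Recruiting from both arms with the 25% reduction in SPARX only: 3,500 × 0.20 × 0.75 × 0.50 + 3,500 × 0.20 × 0.50 = 612.5, not 525.
- SPARX arm without the 25% reduction: 3,500 × 0.20 × 0.50 = 350 entrants and 245 completers, still short.

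**The case against.** The best defence is that the section foresees a shortfall and allows for supplementary participants, that the primary endpoint belongs to Stage I, and that a covariate-adjusted analysis would be more efficient than the change-score calculation.

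Part of this stands. The Stage I comparison is untouched, and baseline adjustment recovers some power. But 65% is still below the 80% set for the trial, and the same adjustment would also lower the detectable effect at 368 completers (0.25), so it does not explain the stated 0.29. The supplementation is discretionary and does not correct the calculation.

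The halving rests on arms of similar size, and 1:1 allocation of schools does not guarantee equal student numbers. Imbalance cannot rescue the figure, however: 525 / (0.20 × 0.75 × 0.50) = 7,000, so the SPARX arm would have to supply every student followed to 12 months.

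Three stronger readings are tempting but unsupported:
- A reader might infer that about half of Stage II would be young people never given SPARX. The article does not say where the additional participants would come from or whether they would receive SPARX first. Entry at Stage I is a possible reading.
- A reader might infer that Stage II would run with only 368 recruits. The section projects 525 entrants, so the ambiguous wording is not a plan to stop at 368.
- A reader might infer that the claim "Power to detect medium-size effects (0.5 SD) in moderation analyses will be maintained for subgroups down to approximately 120 participants" rests on the wrong kind of power. No formula is given and the analyses are called exploratory, so this cannot be established.

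**Conclusion.** The Stage II projection is wrong as written. Its entrants and completers are twice what the design yields on the protocol's own rates: about 262 and 184, not 525 and 368. At 184 completers, power for d = 0.3 is about 53% and the difference detectable at 80% power is about 0.41 (about 65% and 0.36 with baseline adjustment). The result assumes roughly equal arms and takes the stated rates as given. A shortfall against the Stage II target is therefore to be expected even if all 10,000 students are recruited. An unseen analysis plan could not change this, because the article's explicit numbers conflict with its own design.

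**What to change.** 1. Restate Stage II entrants, participants with endpoint data and detectable effect from the intervention arm only, and name the variance used (change score or baseline-adjusted).
2. Reconcile the two uses of 368 and show the derivation. Relabelling 368 as completers is not enough, since the stated inputs give about 352 completers, or about 503 recruits at 30% attrition.
3. Say that the shortfall is expected at full Stage I recruitment on the assumed rates.
4. State where supplementary participants would come from and whether they would have received SPARX, since this could change the Stage II population. If they come from outside the SPARX arm, report the SPARX-arm result separately.
5. Reconcile the Stage II entry threshold: Hypotheses has PHQ-A above 10, the sample size calculation has 10 or more, and the supplementation paragraph has the top 20% of population scores.

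The cost is protocol wording and a less favourable Stage II power statement. Correcting the statement needs no extra participants; restoring the original power would.

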### Hypotheses

The primary hypothesis is that participants allocated to the intervention arm will show a smaller increase in depressive symptoms relative to those in the control group at 12 months, measured using the self-report Patient Health Questionnaire—Adolescent Version (PHQ-A) [38]. Secondary hypotheses are that depressive symptoms will be lower (e.g., show a smaller increase) in the intervention arm relative to the control arm at other assessment points (post intervention, 6, 24, 36, 48 and 60 months). Using the pre-defined clinical cut-off points on the PHQ-A will also allow a comparison between likely cases of depression across the two arms. It is hypothesised that the percentage of depression cases will be lower in the intervention arm relative to the control arm at post intervention, 6, 12, 24, 36, 48 and 60 months. Secondary mental health outcomes are psychological distress, anxiety and insomnia, and are expected to be lower in the intervention arm relative to the control, at post intervention, 12, 24, 36, 48 and 60 months. Additional outcomes including suicidality, substance use and sleep quality will be reported separately.

For participants in the intervention condition who show clinically significant depressive symptoms at 12 months (PHQ-A score > 10) and who enter Stage II of the trial, it is hypothesised that those who receive the Sleep Ninja intervention will report greater decreases in symptoms of depression (primary outcome), anxiety and insomnia (secondary outcomes) from pre to post intervention (Stage II) and from 12 to 24 months (after they receive the Sleep Ninja intervention), relative to the Stage II control arm.

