### Interventions

This trial will involve two interventions: a universal prevention intervention (Stage I; SPARX) and an indicated prevention intervention (Stage II; Sleep Ninja) for participants showing elevated depressive symptoms 12 months after receiving the universal intervention. Participants can begin or continue with any existing treatments during the study, including antidepressants and psychotherapy, and may receive additional support from health professionals if required.

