### Randomisation

For Stage I, cluster randomisation (at the school level) will be employed for administrative convenience, to avoid control condition contamination, and for the ecological validity of providing the intervention at the cluster level. Schools will be randomised after they are recruited into the trial. The trial statistician who is not involved in the day-to-day running of the trial will perform the randomisation, and the identity of the school will be concealed from the statistician.

Schools will be randomised with a 1:1 allocation, as per a computer-generated randomisation schedule. Balance between the trial arms will be achieved by stratifying based on school size, school location (metropolitan vs. regional), school type (co-educational or gender selective) and Index of Community Socio-Educational Advantage (ICSEA) level. For Stage II, individual-level randomisation with a 1:1 allocation using a computer-generated randomisation schedule stratified by gender and depression severity scores will be employed. This procedure is automated through the Black Dog Institute research platform. Permuted block randomisation will be used at both stages but will not be disclosed to ensure concealment. Allocation to arms is not directly communicated to schools. However, because the study has no control intervention, schools, participants and study operational staff will be aware of school allocation to the intervention arm. With the exception of the trial data manager, other individuals not involved in the day-to-day running of the trial will remain blind to allocation. All outcome assessments are conducted electronically and not subject to assessor bias. Unblinding at the conclusion of analysis will be performed by the trial data manager with authorisation from the Trial Steering Committee.

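### The optional Stage II top-up admits young people who need not have had SPARX, conflicts with the stated Stage II population, and could supply about half of Stage II

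*Protocol article*

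**What the plan says.** Four sections of the protocol article place Stage II inside the SPARX arm:

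- The current study: "an individual-level RCT will be conducted within the intervention arm".
- Hypotheses: the Stage II hypothesis is stated "For participants in the intervention condition who show clinically significant depressive symptoms at 12 months (PHQ-A score > 10").
- Interventions: Sleep Ninja is an indicated intervention "for participants showing elevated depressive symptoms 12 months after receiving the universal intervention".
- Sample size: "participants in this stage must meet eligibility requirements regarding elevated symptoms and failure to respond to the first-stage intervention".

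The same Sample size section then provides that, "if the numbers of participants are not sufficient to reach the Stage II target", the trial may consider "supplementing this sample with additional young people specifically targeted based on PHQ-A scores that fall in the top 20% of population scores". The stated purpose is to give Stage II "comparable power to Stage I to detect an intervention effect will be considered". The clause does not say that the added people must have received SPARX, must have failed to respond to it, or must meet the fixed PHQ-A threshold used elsewhere. It does not say where they would come from or how they would be analysed.

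Under Randomisation, Stage II allocation is 1:1 at the individual level, "stratified by gender and depression severity scores will be employed". Source of recruitment is not a stratification factor.

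**The concern.** The two descriptions give different populations. One is a group already exposed to SPARX and still symptomatic. The other is chosen only by where a PHQ-A score falls in the population. The protocol does not reconcile them, yet the clause counts both groups towards the same Stage II power.

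This bears on a stated aim. The Background criticises earlier prevention trials for offering no further step to people whom a first approach has not helped, the Aims section asks about a second intervention a year after SPARX, and the Discussion presents the two-stage design as a novel feature. If people without SPARX exposure enter in numbers, the pooled estimate mixes Sleep Ninja as a second step with Sleep Ninja as a first step. It then describes a population other than the one in the Stage II hypothesis.

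**Working it through.** **Inputs, all from the protocol.** Up to 10,000 Stage I recruits; 1:1 allocation (Trial design); 30% attrition; 20% with PHQ-A ≥ 10; 25% showing a reduction due to SPARX; 50% of those eligible enrolling; Stage II attrition 30%; α = 0.05 two-sided; power 0.80; baseline–endpoint correlation 0.5 (Sample size).

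**Step 1. Reproduce the plan's figures.**
- Entrants: 10,000 × 0.70 × 0.20 × 0.75 × 0.50 = 525. This matches.
- Completers: 525 × 0.70 = 367.5, or 368. This matches.
- SD of change at r = 0.5: √(2 × (1 − 0.5)) = 1.
- Detectable d with 184 per arm: (1.960 + 0.842) × √(2/184) = 0.292. This matches the stated 0.29.

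The 525 starts from 7,000 completers, which is both Stage I arms. Only the SPARX arm can enter Stage II, and a reduction due to SPARX can occur only there.

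**Step 2. Restrict the funnel to the SPARX arm.**
- Entrants: 5,000 × 0.70 × 0.20 × 0.75 × 0.50 = 262.5.
- Completers: 262.5 × 0.70 = 183.75, about 184 in total or 92 per arm.

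**Step 3. Share of Stage II that a top-up would have to supply.** Share = 1 − SPARX-arm entrants / target.

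| Stage I recruits | SPARX-arm entrants | Share, target 525 | Share, target 368 |
|---|---|---|---|
| 10,000 | 262.5 | 50% | 29% |
| 8,000 | 210 | 60% | 43% |
| 5,000 | 131.25 | 75% | 64% |

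The 368 column takes literally the protocol's wording that 368 must be recruited. Applying the Stage I method without the design effect gives 176 per arm, or 352 completers, and 352/0.70 ≈ 503 recruits. With that target the share at 10,000 is 1 − 262.5/503 = 48%.

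**Step 4. What would avoid a shortfall at 10,000 recruits.** The SPARX arm has 3,500 × 0.20 × 0.75 = 525 eligible people.
- Target 525: uptake of 525/525 = 100%, or prevalence of 525/(3,500 × 0.75 × 0.50) = 40% at 50% uptake. Otherwise about 20,000 Stage I recruits.
- Target 368: uptake of 368/525 = 70%, or prevalence of 368/1,312.5 = 28%.

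**Step 5. Power in the SPARX-arm part alone.** Power = Φ(d × √(n/2) − 1.960), with n = 91.875 per arm and SD = 1.
- d = 0.30: Φ(2.033 − 1.960) = 0.53. With 184 per arm it is 0.82.
- Detectable d: 2.802 × √(2/91.875) = 0.41.
- If the analysis gains the full benefit of baseline adjustment (SD = √0.75), power at d = 0.30 is 0.65.

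**Step 6. The three entry rules.** Hypotheses uses a PHQ-A score above 10, the Stage II yield calculation uses 10 or more, and the top-up uses the top 20% of population scores. A score of exactly 10 passes the second rule and fails the first. The third is a percentile with no stated reference population.

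**The case against.** **The top-up is a contingency.** The clause says only that it will be considered, and only if numbers fall short. On the protocol's own funnel there is no shortfall at 10,000 recruits, and the 20% prevalence is described as conservative. This stands as far as it goes: nothing commits the trial to a top-up, and the shares above are what it could be. But the zero shortfall depends on counting the control arm. With the SPARX arm only, prevalence or uptake would have to double to reach 525. The gap is easier to close if 368 is the recruitment target.

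**Stage II stays randomised.** A reader might infer that a top-up would leave Stage II unable to answer its second-step question. The documents do not support that. Allocation is individual and 1:1, so Sleep Ninja versus control is a valid comparison in the pooled sample and also among SPARX-exposed participants. Not stratifying by source causes no bias. The SPARX-arm group would also be just as small without a top-up.

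**Dilution is not shown.** A reader might infer that mixing sources would shrink the estimated effect. The protocol gives no effect for people without SPARX, and its rationale for Sleep Ninja (sleep disturbance as risk factor and symptom) does not depend on earlier SPARX. As an assumption only: with half the sample from each source and d = 0.30 in the SPARX arm, the pooled value is 0.15 if the top-up effect is 0, 0.30 if it is 0.30, and 0.45 if it is 0.60. The direction is unknown.

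**The source is not named.** Drawing from the Stage I control arm is possible under the wording but is not stated.

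**Similar severity.** Since the protocol estimates that 20% score 10 or more, the top 20% may be close to that threshold. This is fair, and it leaves SPARX exposure and non-response as the main mismatch.

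**Left to fuller documents.** Model terms for an optional contingency could sit in a fuller protocol or analysis plan. The conflict in population, however, is written into this article.

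**Conclusion.** The concern holds in a limited form. The top-up clause sets a Stage II population different from the one in The current study, Hypotheses, Interventions and the eligibility statement under Sample size, and the text does not reconcile them. If the top-up is used, the pooled estimate will not be specific to SPARX-arm participants with elevated symptoms.

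At 10,000 recruits the top-up could form about 50% of Stage II against 525 entrants, or 29% against 368, with larger shares if Stage I under-recruits. This assumes the protocol's attrition, prevalence, response and uptake rates, equal Stage I arms, and entry from the SPARX arm only. On the change-score basis that reproduces the plan's d = 0.29, the estimate that does bear on the hypothesis would have about 53% power at d = 0.30.

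The documents do not show that a top-up will happen, that it would invalidate Stage II, or that it would lower the estimated effect. What is at risk is whom the pooled estimate describes, and the precision of the estimate for the intended group.

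**What to change.** 1. Reconcile the top-up clause with the four sections that place Stage II in the SPARX arm, and reconcile the three PHQ-A entry rules.
2. Restate the Stage II yield for the SPARX arm only (about 262 entrants and 184 completers on the current rates), and say whether 368 means recruits or completers.
3. If a top-up is kept:
   - state that it will not be drawn from the Stage I control arm, whose comparison with SPARX runs to 60 months;
   - add source (SPARX arm or top-up) as a Stage II stratification factor;
   - fit source and source-by-arm in the Stage II model;
   - report the SPARX-arm estimate alongside the pooled one, name it as the estimate bearing on the Stage II hypothesis, and state its lower power.

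The cost is one more stratum in a randomisation that is already automated, and two model terms. The stratum must be set before Stage II randomisation begins, because it cannot be added later. The real downside is that the SPARX-arm estimate rests on about half the planned completers. A top-up cannot cure that, and the report should say so.
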